### Data collection and quality control

The data collection and management for this paper are performed using the OpenClinica open-source software for Electronic Data Capture (EDC), version 3.1 (Copyright OpenClinica LLC and collaborators, Waltham, MA, USA, www.OpenClinica.com). Case report forms are filled in for each patient by trained healthcare providers (attendings, residents) or properly trained data managers. Operative and postoperative data are retrieved both from electronic medical charts and administrative databases. Surgical data analysis, including detection of postoperative complications, will be done under the supervision of a staff surgeon.

Quality control and data authenticity will be performed by data managers and clinical research coordinators. Clinical data will be compared to routinely collect administrative information retrieved from regional registries to ensure reliability and completeness and to avoid selection bias. Registration of each patient is automatically linked to the regional administration database, which by law receives notification on all patients deceased in Emilia-Romagna.

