## Statistical considerations

All the analyses will be performed considering tumor location (colon or rectum) as a stratification factor. For continuous variables, the arithmetic mean and standard deviation (SD), as well as the median value and minimum–maximum, will be presented. Absolute frequencies together with the percentage relative frequencies will be reported while summarizing qualitative variables.

To evaluate the performance of surgical activity, absolute numbers and relative percentages of each performance indicator reported will be calculated. The mortality rate will be defined as the number of patients who died within 30, 90, and 180 days after surgery. Graphical representation will also be used: funnel plots will be displayed for each KPI, both in unadjusted and adjusted versions.

Appropriate statistical models (i.e., mixed models, logistical regression, multilevel models) will be developed to evaluate the relationship among analyzed indicators and potential explanatory factors as well as for standardization/adjustment purposes. Main covariates will include age, gender, ASA score, CCI, surgery setting (urgent vs. elective), and ECOG.

Hospitals will be used as random effects to account for the presence of possible variability among hospitals. Other exploratory subgroup analyses will be performed.

Furthermore, to assess the effects of continuous monitoring and benchmarking on clinical outcomes, a before-and-after approach will be used. Specifically, assuming the time from the first subject surgery until the release of the first benchmarking report as the reference period (baseline, i.e., “before” period), the analysis will evaluate any significant changes occurred afterwards. Any changes on the outcomes will be, therefore, attributed to the benchmarking effect.

Missing values will be replaced and estimated using multiple imputations. A two-sided 95% confidence interval (95% CI) will be reported as appropriate.

Statistical analysis will be performed using R statistical software (v. 4.0.6) — www.r-project.org.

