## Discussion

Surgery is the main treatment modality for stages I–III colorectal cancer and frequently represents the most effective choice even in a palliative setting. Despite massive improvements in perioperative care and techniques, colorectal cancer surgery is still associated with a significant burden of postoperative complications which result in greater healthcare costs and severe functional sequalae for patients. If the value of healthcare is maximizing quality care at minimal cost [33], the large-scale participation in an audit, which constantly measure the care quality and the resources used associated for a benchmark feedback, represents a unique opportunity to significantly improve healthcare and limit expenditure.

Administrative data have already revealed their limitations when used to evaluate quality of care and can lead to misinterpretation when used to measure composite postoperative outcomes of complex and/or frail patients [34, 35]. However, together with mortality registries, they are essential for quality check control (enrollment rate) and completeness of data entry for specific items (re-admission rate, emergency department admission after discharge): for this reason, they were integrated into the entire ESCA auditing process.

Clinical data are more difficult and expensive to collect than administrative data, but these challenges are far outweighed by the opportunity clinical data can create in obtaining reliable information on the entire clinical process, ultimately improving quality and reducing hospital costs, as has been demonstrated by previously validated large national clinical audits such as NSQuIP [36] and DCRA [10]. The Dutch experience, thanks to the inclusion of the entire colorectal surgery population, represents to date, the most meaningful one given its “real-world” nature without selection bias and with risk-adjusted outcome data.

ESCA is an initiative which follows one of the main recommendations of the European Cancer Care Organization (ECCO) — Essential Requirements for Quality Cancer Care (ERQCC). The ERQCC recommended that clinical and process outcome data should be systematically measured and collected to give high quality care to patients [37].

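### Crediting any before/after change to benchmarking is unsafe for anastomotic leak and Clavien–Dindo grade, because the first report may change how these are recorded as well as how patients are treated

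*Protocol article*

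**What the plan says.** **The comparison.** Under Statistical considerations, "to assess the effects of continuous monitoring and benchmarking on clinical outcomes, a before-and-after approach will be used". The baseline runs from the first operation to release of the first benchmarking report. The paragraph ends by attributing whatever changes afterwards to benchmarking.

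**The outcomes.** Under Study outcomes, the frequency of complications, re-interventions, re-admissions and death is the primary objective. The effect of monitoring on outcomes is secondary. Leak is KPI 5 and Clavien–Dindo grade ≥3 is KPI 9 (Table 2). On the form, leak is a yes/no item, and the user enters the type and grade of complication (Table 6).

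**Who records.** Under Data collection and quality control: "Case report forms are filled in for each patient by trained healthcare providers (attendings, residents) or properly trained data managers". Also: "Surgical data analysis, including detection of postoperative complications, will be done under the supervision of a staff surgeon". The article does not say which hospital this surgeon belongs to.

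**Checks.** On sources, the same section adds: "Operative and postoperative data are retrieved both from electronic medical charts and administrative databases". It then assigns the checking to staff other than the surgeons: "Quality control and data authenticity will be performed by data managers and clinical research coordinators". An external check against regional sources is planned as well: "Clinical data will be compared to routinely collect administrative information retrieved from regional registries to ensure reliability and completeness and to avoid selection bias". For deaths, registration is linked to a regional database "which by law receives notification on all patients deceased in Emilia-Romagna". The Discussion calls administrative data essential for checking enrolment and for "completeness of data entry for specific items (re-admission rate, emergency department admission after discharge".

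**Feedback.** Each hospital receives an anonymized report every 12 months comparing all centres on the KPIs. Each centre is also to be given its case-mix adjusted outcomes.

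**The concern.** The hospitals that supply the data on leak and grade are the hospitals whose results are compared and fed back. The exposure under study, receiving the report, can therefore act on the measurement as well as on the care. The Introduction itself relies on the idea that people who know they are monitored change their behaviour, and filling in the form is part of that behaviour.

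This is a different problem from secular drift. A step in recording at the release of the report falls exactly at the cut point of the analysis. Case-mix adjustment does not remove it, because the patients have not changed. A time trend does not remove it either, because the trend would attribute the step to the report, as the plan intends for a real effect.

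At stake is a secondary conclusion, but a central one for an audit: whether feedback made surgery safer. Read as written, the attribution sentence would count a recording shift in leak or severe complications as an effect of benchmarking.

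**Working it through.** The article gives no complication rate, power or detectable effect for the before/after comparison, so there is no planned figure to reproduce. The following shows how large a recording shift would have to be to matter.

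**Inputs from the article**
- Recruitment of about 800 patients per year over 54 months (Setting and study population): 800 × 54/12 = 3,600 patients.
- Length of the before period: 18 months (window of the first preliminary analysis) or 12 months (reporting interval).
  - 18 months: 800 × 18/12 = 1,200 before, 3,600 − 1,200 = 2,400 after.
  - 12 months: 800 before, 2,800 after.
- Two-sided 95% confidence intervals, so two-sided 5%.

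**Assumptions, not in the article**
- Grade ≥3 rate of 10% (range 5–15%), truly the same in both periods.
- After the report, the recorded rate is multiplied by 0.9, 0.8 or 0.7 (events lost) or by 1.2 (better capture).
- Patients independent, that is, no clustering within the 7 hospitals.

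**Formula.** With p₁ and p₂ the recorded rates, n₁ and n₂ the period sizes, and p̄ the pooled rate:
- SE₀ = √[p̄(1−p̄)(1/n₁ + 1/n₂)]
- SE₁ = √[p₁(1−p₁)/n₁ + p₂(1−p₂)/n₂]
- chance of a significant result in the stated direction = Φ[(|p₁−p₂| − 1.96·SE₀)/SE₁]

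**One case in full** (10% recorded before, 8% after, 1,200/2,400)
- p̄ = (120 + 192)/3,600 = 0.0867
- SE₀ = √[0.0867 × 0.9133 × (1/1,200 + 1/2,400)] = 0.00995
- SE₁ = √[0.10×0.90/1,200 + 0.08×0.92/2,400] = 0.0103
- Φ[(0.020 − 0.0195)/0.0103] = Φ(0.05) = 52%

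**All cases: chance of a significant false change when care has not changed**

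| n before/after | Assumed rate | 10% lost | 20% lost | 30% lost | 20% gained (false increase) |
|---|---|---|---|---|---|
| 1,200/2,400 | 5% | 10% | 29% | 58% | 22% |
| 1,200/2,400 | 10% | 17% | 52% | 87% | 43% |
| 1,200/2,400 | 15% | 23% | 71% | 97% | 62% |
| 800/2,800 | 5% | 9% | 25% | 50% | 18% |
| 800/2,800 | 10% | 14% | 44% | 78% | 34% |
| 800/2,800 | 15% | 20% | 61% | 92% | 51% |

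With no recording change the chance is 2.5% in each direction. Using the inclusion dates (15 April 2019 to 31 December 2023, about 56.5 months) instead of 54 months moves the 52% only to 53%.

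**Which outcomes are exposed**
- *Death at 30, 90 and 180 days:* reaches the regional database by legal notification, outside the surgical unit. Protected.
- *Readmission:* named in the Discussion as checked for completeness against administrative data. Partly protected.
- *Return to theatre:* an entry on the same form, but a discrete event that the chart can confirm.
- *ICU transfer because of complications:* an entry on the same form, with a judgement about cause.
- *Leak and grade ≥3:* judgement-based form entries, not named in any specific check. Most exposed.

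**The case against.** The safeguards are real. Data managers may complete forms, charts and administrative databases are sources, and separate staff do quality control. The article also condenses a fuller protocol, where leak definitions and training may be set out. This stands, and the point does not rest on the lack of a leak definition. But none of these safeguards is described as grading that is masked to period or independent of the hospital, and the attribution sentence is a positive rule that makes no allowance for recording.

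Four stronger readings are tempting, and the documents do not support them:

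- *That the surgical teams grade their own complications knowing their rank.* Recorders include data managers, the supervising surgeon's hospital is not stated, the reports are anonymized, and no ranking is mentioned. A centre given its own adjusted results can probably place itself, but that is an inference.
- *That the administrative comparison cannot reach leak or grade.* The Methods wording is general. The Discussion names some items without excluding others. Coverage of leak and grade is simply not stated.
- *That complications will appear to fall.* Feedback and cross-checks may equally improve capture and produce an apparent rise.
- *That the primary outcome is invalid.* The primary objective is to describe frequencies. The before/after effect is secondary.

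On size, a modest loss of 10% gives a significant result in only about 10–23% of cases with the 18-month baseline. The plan also stratifies by colon and rectum, which weakens any single test. In the case worked in full, z is about 0.020/0.00995 = 2.0, and a stratum with an assumed 70% of patients would have z of about 2.0 × √0.70 = 1.7. This too stands. It limits how often a false change would reach significance, but the estimate remains biased.

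**Conclusion.** The concern holds for anastomotic leak and Clavien–Dindo grade. A before/after change in either, up or down, cannot be told apart from a shift in recording that begins with the first report, so it cannot be credited to benchmarking automatically. It does not hold for mortality, and holds only in part for readmission.

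Under the stated assumptions, a 20% loss of recorded severe complications gives a 29–71% chance of a significant false reduction with the 18-month baseline, and 25–61% with the 12-month baseline, against a nominal 2.5%. At a 10% rate, a 20% gain in capture gives a 43% or 34% chance of a significant false increase. The rates and recording shifts are assumed, and clustering is ignored. The figures show that a moderate shift would be enough. They do not show that one will occur.

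**What to change.** 1. **Replace the closing sentence of the before-and-after paragraph** in Statistical considerations. The new text should say that the conclusion on benchmarking rests mainly on linked 30-, 90- and 180-day mortality and on readmission verified against administrative data. Unplanned return to theatre within 30 days may be added as a discrete, chart-verifiable event, with a note that it is still recorded on the form.
2. **Report before/after changes in leak and grade ≥3 as supportive**, and state that they are open to a change in recording in either direction.
3. **Add one concordance table.** By period and hospital, with 95% CI, give the proportion of patients with a 30-day unplanned return to theatre, ICU transfer because of complications, or death within 30 days who have no recorded grade ≥3 complication. The Table 6 re-intervention item is not limited to unplanned returns, so use the recorded reason to identify them.
4. **Interpret changes in complications in the light of that table, without an automatic veto.** Some discordance is legitimate, such as a death recorded as disease progression (Table 8), and a small rise may be chance.

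The cost is a few sentences and one cross-tabulation of fields already collected in Tables 6 and 8. The price is a narrower claim: complications managed without a return to theatre, ICU transfer or readmission would support the conclusion but not carry it.

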### Study variables

The full data set is composed of up to 172 possible variables, and it is organized in sections as follows.

#### Preoperative assessment

Preoperative functional assessment is conducted using the Eastern Collaborative Oncology Group Performance Status (ECOG PS) [16] and the American Society of Anaesthesiology (ASA) score [17, 18]. Patients aged ≥ 70 years are screened for frailty with the Katz Activities of Daily Living (ADL) [19] and the Flemish version of the Triage Risk Screening Tool (fTRST) [20, 21]. Comorbidities are assessed using the age adjusted Charlson Comorbidity Index (CCI) [22, 23] and the presence of malnourishment is evaluated using the nutritional risk score (NRS) [24]. All screening tests are reported in detail in Table 3. Baseline evaluation further includes information on the living conditions before surgery and polypharmacy.

**Table 3 Tab3:** Preoperative functional status assessment tools

Test	Range
American Society of Anaesthesiologists (ASA) score	1–5
Eastern Collaborative Oncology Group Performance Status (ECOG-PS)	0–5
Katz Activities of Daily Living (ADL)	0–6
Flemish version of the Triage Risk Screening Tool (fTRST)	0–6
Nutritional risk screening (NRS)	0–3
Age-adjusted Charlson Comorbidity Index (CCI)	0–38

The diagnostic work-up is then assessed including the following items:Number and location of primary cancer;Presence/absence of distant metastases;Date of preoperative endoscopy and pathology report of biopsy;Presence of cancer-related preoperative complications (anemia, colonic obstruction, perforation);Date and type of preoperative imaging studies (CT scan, MRI, PET-CT) as appropriate.

For rectal cancer patients undergoing pelvic MRI and/or neoadjuvant treatments, specific items will be also collected as reported in Table 4.

**Table 4 Tab4:** Pelvic MRI features for rectal cancer and type of neoadjuvant treatment

PREOPERATIVE PELVIC MRI	POSSIBLE ANSWERS
Mucinous features	yes/no
Distance from anal verge	value [mm]
Distance from pubo-rectal sling	value [mm]
Cranio-caudal extension	value [mm]
Presence of extra-mural vascular invasion (EMVI)	yes/no
Invasive margin site assessed?	yes/no
Invasive margin site location	Anterior Posterior Right lateral Left lateral Circumferential
Mesorectal extra-mural invasion and depth	yes/no [mm]
Lymph node status	N0/N+
Minimal distance from mesorectal fascia	value [mm]
Location of minimal distance from mesorectal fascia	Anterior Posterior Right lateral Left lateral
mrTNM	[User should report the tumour node metastasis staging]

TYPE OF NEOADJUVANT TREATMENT	
Short course radiation therapy (5×5)	yes/no
Standard long course chemo-radiotherapy	yes/no
Total neoadjuvant therapy (TNT)	yes/no
Chemotherapy alone	yes/no

RESTAGING PELVIC MRI	
Mucinous features	yes/no
Distance from anal verge	value [mm]
Distance from puborectal sling	value [mm]
Cranio-caudal extension	value [mm]
Presence of EMVI	yes/no
Invasive margin site assessed?	yes/no
Invasive margin site location	Anterior Posterior Right lateral Left lateral Circumferential
Mesorectal extra-mural invasion and depth	yes/no [mm]
Location of minimal distance from mesorectal fascia	Anterior Posterior Right lateral Left lateral
Lymph node status	N0/N+/na
Minimal distance from mesorectal fascia	value [mm]
Location of minimal distance from mesorectal fascia	Anterior Posterior Right lateral Left lateral
ymrTNM	[User should report the tumour-node-metastasis staging after neoadjuvant treatment]

#### Surgery

Type of surgical procedure, regimen, length of surgery, and operative technique is collected. Possible intraoperative complications are identified and specified as well as the need for intraoperative blood transfusions. The radicality of surgery is assessed as well as type of anastomosis including characteristics and technique. If stoma is created, details are reported as appropriate. All surgical items are reported in detail in Table 5.

**Table 5 Tab5:** Surgical variables

SURGERY	POSSIBLE ANSWERS
Colonic stent preoperatively placed?	yes/no
Surgical regimen	Elective Urgent Unknown
Surgical intent	Curative Palliative Unknown
Surgical technique	Laparotomy Laparoscopy Robotic TEM Transanal open TAMIS taTME Unknown
Conversion	yes/no
Time to conversion	Early (< 60 minutes) Late (> 60 minutes)
Reason of conversion	Reactive Strategic
Surgical procedure	Ileo-cecal resection Right colectomy Extended right colectomy Transverse colon resection Splenic flexure resection Left colectomy Low anterior resection with PME Sigmoid resection Subtotal colectomy Abdomino-perineal excision Total proctocolectomy Transanal local excision Explorative procedure
Type of abdomino-perineal resection:	Standard APR (APE) Extralevator APR (ELAPE) Pelvic exenteration Beyond TME (APR with sacrectomy)
Type of pelvic exenteration: (specify organ included into the resection)	Cystectomy Prostatectomy Istero-annessectomy
Intra-operative complications	yes/no
Type of Intra-operative complication	Splenic injury Biliary injury Small bowel injury Vaginal injury Urological injury Peritoneal perforation during transanal procedure
Additional resections	Ileal resection Minor hepatic resection Major hepatic resection Other abdominal/pelvic organs Peritonectomy (including HIPEC) Lung resection Other (specify)
Intra-operative blood transfusion?	yes/no
Length of surgery	value [minutes]
Radicality	R0/R1/R2
Anastomosis	yes/no
Type of anastomosis—1	Hand-sewn Stapled
Type of anastomosis—2	Ileo-colonic Colo-colonic Colo-rectal Ileo-rectal Colo-anal Ileo-anal
Type of anastomosis—3	Intra-corporeal Extra-corporeal Not applicable
Stoma?	yes/no
Type of stoma	End ileostomy End colostomy Loop ileostomy Loop colostomy

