### Key performance indicators, case-mix, benchmarking, and feed-back activity

A core set of key performance indicators (KPIs) will be assessed to measure performance and evaluate the quality of colorectal cancer surgery across the participating centers (Table 2). Each KPI will be estimated both as unadjusted and risk adjusted for differences in patients’ characteristics for a fair comparison among the participating hospitals.

**Table 2 Tab2:** Overview of the selected key performance indicators

**ID**	**Indicator title**	**Indicator description**	**Indicator type**
1	Multidisciplinary discussion	Rate of patients discussed at a multidisciplinary meeting (MDM) before surgery	Colon and rectal cancer
2	Neoadjuvant treatment	Rate of patients receiving neoadjuvant treatment (radiation therapy, chemo-radiation, chemotherapy, total neoadjuvant treatment)	Rectal cancer
3	Minimally invasive resections	Rate of patients undergoing minimally invasive resection	Colon and rectal cancer
4	Conversion	Conversion rate from minimally invasive to open surgery at any time during the procedure	Colon and rectal cancer
5	Anastomotic leak	Rate of anastomotic leakage	Colon and rectal cancer
6	Anastomosis	Rate of patients undergoing anastomosis after low anterior resection	Rectal cancer
7	Loop ileostomy	Rate of loop ileostomy creation after low anterior resection	Rectal cancer
8	Length of stay (LOS)	Rate of patients discharged within postoperative days 3 and 5	Colon and rectal cancer
9	Postoperative complications	Rate of patients with severe postoperative complications (grade ≥ 3 according to Clavien–Dindo classification)	Colon and rectal cancer
10	Quality of total mesorectal excision (TME)	Rate of patients with TME grade 1 or 2	Rectal cancer
11	Positive circumferential resection margins (CRM)	Rate of reported positive CRMs (less than or equal to 1 mm)	Rectal cancer
12	Lymph-nodes yield	Rate of patients for who received adequate lymphadenectomy (≥ 12 lymph-nodes)	Colon and rectal cancer
13	Unplanned reintervention	Rate of patients with an unplanned return to theatre within 30 days after index surgery	Colon and rectal cancer
14	Unplanned readmission	Rate of patients with unplanned readmission within 30 days after discharge/transfer from surgical unit	Colon and rectal cancer
15	Postoperative mortality	Rate of patients who died 30,90, or 180 days after surgery	Colon and rectal cancer

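### Table 5 offers low anterior resection only with PME, so the low anterior resection denominator of KPIs 6 and 7 is ambiguous and PME and TME cannot be told apart by procedure code

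*Protocol article*

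**What the plan says.** The Surgery section of the protocol article presents Table 5 as complete: "All surgical items are reported in detail in Table 5". The surgical procedure row has thirteen options. After five colonic entries it continues: "Left colectomy Low anterior resection with PME Sigmoid resection Subtotal colectomy Abdomino-perineal excision Total proctocolectomy Transanal local excision Explorative procedure". The only low anterior resection is therefore "Low anterior resection with PME". There is no entry with TME, no unqualified low anterior resection and no option for other procedures.

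Table 2 (Key performance indicators section) builds two rectal cancer indicators on that operation without splitting it by mesorectal extent. KPI 6 is "Rate of patients undergoing anastomosis after low anterior resection" and KPI 7 is "Rate of loop ileostomy creation after low anterior resection".

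TME does appear elsewhere. The technique row of Table 5 includes a transanal TME option ("Laparotomy Laparoscopy Robotic TEM Transanal open TAMIS taTME Unknown"). One abdomino-perineal subtype refers to surgery beyond TME. KPI 10 is "Rate of patients with TME grade 1 or 2", and its source is the Quirke grade among the rectal cancer pathology items in Table 7. The Key performance indicators section also names type of surgery as one of the case-mix variables for comparing hospitals.

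**The concern.** The qualifier on the single entry makes sense only as a contrast with TME, and that contrast is missing from the list. An ordinary open, laparoscopic or robotic sphincter-preserving resection with TME has no correct code. The person completing the form has three ways out: use the PME entry, choose a different procedure, or leave the item blank. The article states no rule for choosing between them.

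Two things are at stake for KPIs 6 and 7, which are fed back to hospitals every year and shown in funnel plots. If hospitals resolve the gap differently, their denominators contain different kinds of patients. If they all use the PME entry, the denominator is whole, but procedure code no longer says which operation was done. The type-of-surgery adjustment then cannot use that distinction. This is a data-capture matter, so an analysis plan cannot restore what the form did not record.

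**Working it through.** The article gives no figure to reproduce. The check traces each indicator to its fields.

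| Indicator | Numerator field | Denominator field | Effect of the gap |
|---|---|---|---|
| KPI 6 | Anastomosis yes/no, Table 5 | Low anterior resection, Table 5 procedure list | Denominator ambiguous |
| KPI 7 | Loop ileostomy under type of stoma, Table 5 | Low anterior resection, Table 5 procedure list | Denominator ambiguous |
| KPI 10 | Quirke grade, Table 7 | Rectal cancer patients, Table 7 pathology items | None; no procedure code needed |

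For KPIs 6 and 7 both numerators are collected. The denominator rests on one code whose label, read literally, excludes TME.

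**Illustration, on assumptions only.** Let *s* be a hospital's share of TME among its low anterior resections, *p* the loop ileostomy rate after PME and *t* the rate after TME. None of these is in the article. Assume *p* and *t* are the same in every hospital, so practice is identical. If all low anterior resections are entered under the single code, unadjusted KPI 7 is *s·t* + (1 − *s*)·*p*.

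*Same coding, different case mix (s = 30% and 60%):*
- *p* = 10%, *t* = 70%: 0.3×70 + 0.7×10 = 28% and 0.6×70 + 0.4×10 = 46%, a gap of 18 points.
- *p* = 20%, *t* = 50%: 0.3×50 + 0.7×20 = 29% and 0.6×50 + 0.4×20 = 38%, a gap of 9 points.

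*Same case mix, different coding (s = 30% in both hospitals):* one hospital enters every case under the code; the other enters only true PME there and places TME elsewhere. The second hospital then shows *p*.
- *p* = 10%, *t* = 70%: 28% against 10%, a gap of 18 points.
- *p* = 20%, *t* = 50%: 29% against 20%, a gap of 9 points.

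The two ranges coincide because both gaps equal 0.30 × (*t* − *p*). The first could be reduced by adjusting for PME/TME if that were recorded. The second could not be adjusted away, because the missing patients are outside the denominator.

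**The case against.** The strongest case on the other side has four parts.

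**The KPIs can be computed.** A reader might infer that KPIs 6, 7 and 10 cannot be calculated, or that TME resections have no code at all. The article does not support either. KPIs 6 and 7 are defined on low anterior resection as a whole, and if every site uses the single entry for every such operation they are computable exactly as defined. KPI 10 comes from pathology. Abdomino-perineal excision has its own code, and transanal TME is recordable as a technique. All of this stands. What remains is that no rule tells sites to use the entry that way, and its label tells them otherwise.

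**Other fields can stand in.** Tumour location, MRI distance from the anal verge and type of anastomosis (colo-rectal or colo-anal) are collected, and every KPI is also reported risk adjusted. This stands in part. The MRI distance exists only for patients who had that imaging, type of anastomosis only for those anastomosed, and the technique field marks only the transanal approach. The main covariates named under Statistical considerations are age, gender, ASA, CCI, urgency and ECOG. That list is not stated to be exhaustive, but it contains neither tumour height nor mesorectal extent.

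**It may be a printing slip.** Nearby tables have slips of the same kind: the TME grade list in Table 7 prints grade 1 twice, and Table 8 repeats the 30-day status label under the 90- and 180-day headings. The full case report form is not shown, and a list entry lost when the table was read by a program cannot be excluded. This stands, and it is why the first step of the fix is a check.

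**Separate reporting by PME and TME is a preference.** This also stands. Table 2 sets these KPIs on low anterior resection as a whole, and nothing in the article requires splitting them.

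**Conclusion.** The point holds as an inconsistency between Table 5 and Table 2. As printed, low anterior resection with TME has no procedure code. The denominators of KPIs 6 and 7 can therefore differ between hospitals, and PME and TME cannot be separated by procedure code for case-mix adjustment. It is worth correcting because between-hospital comparison is the purpose of these indicators.

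The size is not known. The 9 to 18 points are an unadjusted illustration on assumed diversion rates and TME shares. They should not be read as an estimate for these seven hospitals, nor as what would remain after risk adjustment. The conclusion assumes that the live form carries the same list as the article, which cannot be confirmed from the article alone.

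**What to change.** Compare the Table 5 procedure list with the live case report form.

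- **If the option is missing from the form:** add an entry for low anterior resection with TME beside the PME entry. Recode from the operative report the low anterior resections already entered, including rectal cancer cases placed under another procedure or left blank. State in Table 2 that the denominator of KPIs 6 and 7 is both codes together, and use PME/TME as a case-mix variable for these two indicators.
- **If the option is present in the form:** correct Table 5. No recoding is needed.

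The cost is one added answer and a small recoding effort in the first case, and a table correction in the second. Keeping both codes in one denominator leaves the KPI definitions as they are and does not thin the cells.
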